### Measures

Data are obtained from patient questionnaires, physician questionnaire after completed encounter, and encounter chart review. For several measures, similar information is gathered from all three sources. Literature on agreement among these three sources of information in a variety of settings typically suggests only modest agreement [67-70]. For most assessments, the primary measurement source will be considered patient report, which may be more closely associated with outcomes [68]. Based on the theoretical framework of the intervention, the effects of the intervention will depend on the extent to which patients perceive (and recall) specific aspects of encounters. Thus, even if the physician correctly recalls an aspect of the encounter (for example a recommendation for treatment), it is still critical for that recommendation to be perceived by the patient as sufficiently salient to result in patient recall of the recommendation. Chart documentation presumably reflects issues thought important enough by the doctor to document in the chart. But again, unless those issues are effectively communicated to the patient they are less likely to affect patient recall.

The outcome measures, measurement points, and assessment methods for the two sub-studies are summarized in Table 1. When a construct is also measured at baseline (pre-intervention), the same variable definitions are used.

**Table 1 T1:** RCT Sub-studies and Process and Outcome Measures

	**Measurement points**		**Method(s) of measurement**
	**Immediately after index office visit**	**12 week follow-up**	

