### Procedures for telephone screening interview for eligibility and sampling of patients

Primary screening for patient eligibility was conducted using a short telephone interview administered one to two weeks before the patient’s next scheduled primary care visit. Patient eligibility was based on: the ability to read and understand English; the ability to use a computer program, and the patient’s self-report that he/she was not currently taking medication for depression. In order to enrich the sample with more severely depressed patients, all patients with a PHQ-8 score of 10 or more were invited to participate. For those patients having a PHQ-8 score of less than 10, a custom programmed computer software application was used to randomly sample patients for inclusion in the study. Patients were sampled independently with varying probabilities (Poisson sampling) according to their PHQ-8 score category and the calendar time of screening, with the sampling probabilities updated occasionally to help ensure that the study would accrue the target total sample of 308 in the non-depressed group. Eligible patients who verbally agreed to participate in the study at the end of the screening interview were invited to a research appointment on the day of their scheduled primary care visit.

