### Randomization

The unit of randomization was the patient. We chose to randomize individual patients rather than physicians because the intervention was intended to operate at the patient level (affecting patient knowledge, attitudes, self-efficacy, and behaviors) and because the improved precision of estimated intervention effects that arises from randomizing patients from the same physician to different study arms was felt to outweigh the increased risk of bias from between-arm contamination that arises from communication among patients.

During the previsit computer session, patients were randomized to an intervention after answering questions about their gender and race/ethnicity, via a computerized randomization algorithm incorporated into the multi-media computer interface. To ensure balanced assignment by gender and race/ethnicity, the computer randomization program stratified subjects into one of eight groups: black female, black male, Hispanic female, Hispanic male, white female, white male, other female, other male. Computerized racial/ethnic group assignment was based on the following decision rule: 1) Hispanic trumps all other selections, 2) for non-Hispanics, African-American trumps all (e.g., someone selecting African-American and Asian for race would be put into the African-American randomization category); and 3) for people not selecting black, “other” categories trump white (e.g., if someone selects Native American and white, they are randomized as other). Within each of these eight categories, patients were randomly allocated in equal proportions to one of the three study arms, in randomly permuted blocks of nine subjects.

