### Patient accrual and study flow

Altogether, 867 patients were accrued into the study and randomized successfully (Figure 2), 559 with PHQ-9 scores ≥ 5 for Sub-study 1 and 308 with PHQ-9 scores <5 for Sub-study 2 (Table 2). Randomization was generally successful, with modest between-group differences in baseline characteristics (Table 2).

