### Planned analytic approach

For all outcomes except for antidepressant behavior in the non-depressed patients, analyses will be implemented using multiple regression models for clustered data to account for the nesting of patient-level observations within providers and, for longitudinally assessed outcomes, the nesting of repeated measures within patients. Most analyses will take the form of generalized linear mixed models [73], with logistic regression models estimated via generalized estimating equations [74] used as a robust backup in case mixed-model assumptions are violated or computational difficulties (lack of convergence) are encountered.

In generalized linear mixed models, random effects will be specified for the physician (to account for the nesting of patients within physician). For longitudinal outcomes, random effects will also be specified for patient. The key independent variable will be the study group assignment (control vs. PSA vs. IMCP) and additional independent variables will be included to account for the stratified study design. Wald tests, point estimates and 95% Confidence Intervals will be used to assess hypothesized contrasts among the study arms.

Because the incidence of antidepressant behavior in the non-depressed patients is expected to be very low and the primary contrast of interest is for testing the one-sided noninferiority hypothesis that the incidence is not 3.5 percentage points higher in the combined PSA/IMCP groups versus the control, we will use restricted maximum likelihood methods to construct a 2-sided 90% confidence interval for the PSA/IMCP vs. Control risk difference in antidepressant prescribing risk to assess this null hypothesis, as described by Farrington and Manning [72].

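### The regression models name no baseline severity or baseline outcome value as a covariate, which gives up precision, mainly for the continuous outcomes

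*Protocol article*

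**What the plan says.** The article describes generalized linear mixed models with a physician random effect. Study arm is the key fixed effect, and "additional independent variables will be included to account for the stratified study design". For outcomes measured more than once, "For longitudinal outcomes, random effects will also be specified for patient". The one stated exception is antidepressant prescribing in Sub-study 2, which has its own noninferiority method (Farrington-Manning).

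Under Randomization, "To ensure balanced assignment by gender and race/ethnicity, the computer randomization program stratified subjects into one of eight groups", formed from gender and race/ethnicity. Depression severity is not a randomization stratum. Severity does enter the sampling: "Patients were sampled independently with varying probabilities (Poisson sampling) according to their PHQ-8 score category". It also defines the two sub-studies (PHQ-9 of 5 or more, and below 5) and the CIDC population (PHQ-9 of 10 or more).

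On baseline data, the Measures section says "When a construct is also measured at baseline (pre-intervention), the same variable definitions are used". The post-randomization procedures state that the previsit questions are answered before the assigned material is viewed. Table 2 reports PHQ-8, PHQ-9 category, SF-12 mental and physical scores, stigma and communication self-efficacy at baseline. The accrual section comments: "Randomization was generally successful, with modest between-group differences in baseline characteristics (Table 2").

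**The concern.** A patient's score before the visit usually predicts the score 12 weeks later better than gender or race/ethnicity does. The article gives a reason for adding covariates (the stratified design), but that reason covers neither PHQ-9 nor the baseline value of the outcome. If the models are fitted as described, outcome variance that those measurements could explain stays in the error term. Intervals are then wider and power lower than the data allow.

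The wording also leaves a choice open. Arm-level baseline differences are already published in Table 2, so covariates settled later would be settled with those differences in view. Naming them now, on prognostic grounds, removes that doubt.

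**Working it through.** **1. The plan's own figure.** Inputs from Power calculations and sample size: 170 per arm, 0.3 sd, two-sided alpha 5%, 80% power.
- Power = Φ(0.3 × √(170/2) − 1.96) = Φ(2.766 − 1.960) = Φ(0.806) = 79%.
- n per arm for 80% = 2 × (1.960 + 0.842)² / 0.3² = 174.4, so 175.

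The stated figure reproduces without covariate adjustment, within rounding. No stated power figure is wrong.

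**2. Gain for a continuous outcome.** Adjusting for a baseline with correlation r multiplies the error variance by 1 − r². The article gives no baseline-to-12-week correlation, so r is assumed. Table 2 gives PHQ-8 correlations of 0.84 to 0.86 between enrollment and index visit. Screening took place one to two weeks before the visit, so a lower value at 12 weeks is to be expected.

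| r (assumed) | 1 − r² | n per arm for 80% | Power at 170 | Detectable difference at 80% |
|---|---|---|---|---|
| 0 | 1.00 | 175 | 79% | 0.30 sd |
| 0.4 | 0.84 | 147 | 85% | 0.28 sd |
| 0.5 | 0.75 | 131 | 89% | 0.26 sd |
| 0.6 | 0.64 | 112 | 93% | 0.24 sd |

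**3. Gain for CIDC.** Counts from Table 2 for IMCP/PSA/control: PHQ-9 10-14 is 66/43/56 and 15+ is 39/31/33. The CIDC population is therefore 105/74/89, total 268.
- Share with 15+: 39/105 = 37%, 31/74 = 42%, 33/89 = 37% (chi-square p = 0.77).
- Assume treatment rates of 25% (10-14) and 45% (15+), the same in every arm. Expected CIDC from case mix alone: IMCP (66 × 0.25 + 39 × 0.45)/105 = 32.4%; PSA (43 × 0.25 + 31 × 0.45)/74 = 33.4%; control (56 × 0.25 + 33 × 0.45)/89 = 32.4%.
- Variance explained by band: overall 15+ share 103/268 = 0.384; overall rate 0.25 + 0.20 × 0.384 = 0.327. Then 0.384 × 0.616 × 0.20² / (0.327 × 0.673) = 0.0095/0.220 = about 4%.

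Neither the imbalance nor the gain in precision is large for the key outcome.

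**4. Size of the chance imbalance.** In all 867 patients, IMCP and PSA differ by (7.9 − 6.7)/5.4 = 0.22 sd on PHQ-8 at the index visit and by (47.7 − 44.8)/12.04 = 0.24 sd on the SF-12 mental score. These figures pool two sub-studies that are analysed separately. Within Sub-study 1 (204/177/178) the PHQ-9 bands do not differ clearly (p = 0.35). Assigning 7, 12 and 18 to the bands 5-9, 10-14 and 15+ gives means of about 10.7/10.1/10.6. The IMCP-PSA gap is then about 0.58 points. The sd of those band scores over all 559 patients is about 4.2, so the gap is about 0.14 sd. At r of 0.4 to 0.6 it would move a follow-up-only contrast by about 0.06 to 0.08 sd. The band scores are assumed, and no sd within the sub-study is reported.

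**5. Which outcomes the text leaves without a baseline term.** PHQ-8, stigma and self-efficacy have two post-baseline points in Table 1 and fall under the patient random effect. Their baseline could enter as a further repeated measure, but no time or arm-by-time term is named. If baseline rows entered with an arm effect alone, that effect would average in the pre-intervention difference. SF-12 has one post-baseline point (12 weeks), and CIDC, follow-up interval and suicide inquiry are single index-visit outcomes. For these nothing in the text brings in a baseline value.

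**The case against.** The strongest reply is that the covariate sentence is not exclusive. This is a condensed article, and a full covariate list is commonly left to an analysis plan that is not shown. A reader might infer that the models adjust for gender and race/ethnicity only and that no model uses baseline values. The text does not say that. The stratified design is not defined in the analysis section either, and sampling by PHQ-8 category could be meant. The hypothesis of greater improvement at 12 weeks also suggests a comparison with baseline. All of this stands. It limits the point to what the text names and leaves open. What remains is that the article does address covariates and gives a reason for them that does not reach severity or baseline outcome values.

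A reader might also infer from Table 2 that unadjusted contrasts would be biased. They would not. Chance imbalance after concealed randomization shifts the estimate in this particular sample but does not bias the randomized estimator, and baseline p-values are a poor guide to choosing covariates. The 0.22 and 0.24 sd gaps also belong to a pooled population for which no analysis is described.

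A third tempting inference is that the key outcome is distorted or badly short of precision for want of a severity term. Step 3 does not support it: case mix alone gives equal rates for IMCP and control and a difference of about 1 point for PSA, and restricting CIDC to PHQ-9 of 10 or more already removes much of the severity variation.

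**Conclusion.** The point holds as one of precision and clarity. The analysis section names arm and design variables, and it names no baseline severity or baseline outcome value. For continuous outcomes, adjustment would raise power for 0.3 sd at 170 per arm from 79% to about 85-93%, if the baseline correlates 0.4 to 0.6 with the outcome. That correlation is an assumption. The comparison is with a follow-up-only model, so the gain is smaller or nil for any outcome whose baseline already enters as a repeated measure. For CIDC the gain is small, about 4% of variance under assumed rates of 25% and 45%. The documents do not support a claim of bias, of an imbalance that threatens CIDC, or of a wrong sample size. The change is worth making because it costs nothing in data, but it does not put the trial's conclusions at risk.

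**What to change.** In the regression models of Planned analytic approach, but not in the Farrington-Manning noninferiority comparison:

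- Prespecify previsit PHQ-9 as a continuous covariate and, where it was measured, the baseline value of the outcome being analysed (PHQ-8, SF-12 mental or physical score, stigma, self-efficacy), besides the gender-by-race/ethnicity strata. Give prognostic value as the reason, not the Table 2 p-values.
- For repeatedly measured outcomes, say whether baseline enters as a covariate or as a repeated measure with its mean constrained to be equal across arms.
- Use a simple baseline imputation for the 867 − 840 = 27 missing SF-12 baselines, so that adjustment drops no patient.
- Report CIDC as a standardised (marginal) risk difference, so that the adjusted result is on the percentage-point scale used for the power calculation.

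The cost is a few sentences of analysis text. Every covariate is already collected, and the sample size statement need not change.

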### Power calculations and sample size

By setting target sample sizes of 170 subjects per arm, the effectiveness sub-study was designed to provide 80% power to detect between-arm (pairwise) differences in the proportion receiving CIDC of 15 percentage points and standardized differences of 0.3 standard deviations (sd) in the mean levels of continuous outcomes, under two-sided testing with alpha = 5% [71]. For the sub-study focusing on non-depressed patients, the target enrollment of 102 subjects per arm provides 80% power to reject the noninferiority null hypothesis that exposure to an experimental intervention groups (N = 204 in the PSA/IMCP groups) is associated with at least a 3.5 percentage point increase in the extremely low risk anticipated for antidepressant prescribing in the control group (N = 102), under one-sided testing with alpha = 5% and assuming that the true risk is 1% in each of the three groups [72]. For pairwise comparisons of means, a sample size of 102 in each arm of the non-depressed sub-study provides greater than 80% power to detect differences of 0.4 sd [71].

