This project’s emphasis on initial care of depression is based on evidence that depression in primary care often goes undiagnosed [13], that clinically mild depression not infrequently evolves to major depression within a year [21], and that even detected depression is often under-treated in primary care [22,23]. Although subsequent care (including attention to patient adherence, careful monitoring of depression treatment response, and avoidance of clinical inertia) is critically important, none of this is possible in the absence of accurate diagnosis and appropriate initial care.

In conducting the trial, we encountered several noteworthy challenges and limitations:

•To accrue the 867 patients ultimately enrolled in the study, we attempted to reach more than 15,000 patients by telephone and screened over 6000. In settings where local ethics boards required an opt-out process prior to any telephone contact (allowing patients to return a postcard indicating their desire not to be screened), screening was even less efficient. Yet we were ultimately successful in enrolling a sample that appears representative of the underlying population of interest, at least in the clinics studied.

•Our protocol required a substantial time investment by patients, as they were required to arrive in clinic one hour prior to their scheduled appointment. In a small proportion of encounters, patients arrived too late to administer the intervention and accompanying surveys, and they had to be rescheduled. Most of the pre-visit time required of patients was for informed consent and survey administration; the PSA and control videotapes were less than three minutes in length, and the median time patients spent with the IMCP was 5 minutes.

•Enrollment was limited to English-speaking patients, and English-speaking Latinos constituted less than 10% of the sample. Generalizability of the findings to this important demographic group will be restricted.

In summary, the results of this RCT will address the question of whether multimedia patient engagement programs for depression improve processes and outcomes of care for depressed persons. In addition, the trial will compare the relative effectiveness of targeted versus tailored interventions. Finally, the study will address whether the interventions are “safe” (i.e. that they do not worsen processes or outcomes of care) and could even have benefits (e.g. fostering less stigmatized views of depression) among non-depressed persons.

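### The one stated noninferiority contrast for antidepressant prescribing pools PSA and IMCP, so it supports a conclusion about their average and not about either programme

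*Protocol article*

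**What the plan says.** The Power section sizes the sub-study for one noninferiority test. Its null hypothesis concerns "exposure to an experimental intervention groups (N = 204 in the PSA/IMCP groups"), set against 102 controls, with a margin of 3.5 points in prescribing risk. Power is put at 80%, "under one-sided testing with alpha = 5% and assuming that the true risk is 1% in each of the three groups".

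Planned analytic approach keeps the same contrast, calls it the primary one, and words the hypothesis as "the incidence is not 3.5 percentage points higher in the combined PSA/IMCP groups versus the control". To assess it, the plan is to "construct a 2-sided 90% confidence interval for the PSA/IMCP vs. Control risk difference in antidepressant prescribing risk" by the Farrington-Manning restricted maximum likelihood method. The regression models with a three-level group factor (control, PSA, IMCP) are used "For all outcomes except for antidepressant behavior in the non-depressed patients". The article therefore states no per-arm contrast for this outcome.

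The aims of Sub-study 2 word the harm hypothesis for the active interventions in the plural. The Discussion says the study will address whether the interventions are safe, meaning "that they do not worsen processes or outcomes of care". Elsewhere the two are separate arms: efficacy is powered pairwise, and the Discussion promises a comparison of targeted with tailored.

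**The concern.** The two programmes differ in kind. PSA is a targeted video of about 2.5 minutes. IMCP is a tailored interactive programme with a median viewing time of 5 minutes (2 at the 10th percentile, 15 at the 90th). The article gives no argument that they carry the same risk of unnecessary prescribing.

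A practice would probably adopt one of them. An upper limit below 3.5 points for the pooled difference bounds a weighted average of two effects. One programme can lie at or above the margin while the average lies well below it. If the pooled result were read as clearing each programme, the chance of wrongly clearing one of them could be several times the nominal 5%.

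**Working it through.** **Inputs.** Margin 3.5 points, one-sided alpha 5%, true risk 1% in every group, 102 per arm and so 204 v 102 (Power calculations and sample size). Achieved non-depressed numbers: IMCP 90, PSA 109, control 109 (Table 2, PHQ-9 category <5), so 199 v 109 pooled. Risks other than 1% are my assumptions, because the article gives none.

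**1. Reproduce the stated power.** Farrington-Manning:

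power = Φ{[δ − (pT − pC) − 1.645·σ0] / σ1}

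- The restricted estimates at δ = 0.035 are 0.0389 (active) and 0.0039 (control).
- σ0 = √(0.0389×0.9611/204 + 0.0039×0.9961/102) = 0.0149.
- σ1 = √(0.0099/204 + 0.0099/102) = 0.01207.
- (0.035 − 0.0245)/0.01207 = 0.87, so power = 80.8%, against 80% stated.

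Exact binomial enumeration of the same test gives 85.6%, and 83.1% at 199 v 109. All pass rates below are exact.

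**2. Error rate under the test's own null.** With both programmes at 4.5% and control at 1%, it passes 5.6% of the time at planned sizes and 4.3% at achieved sizes. It is adequately controlled for the average.

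**3. One programme at the margin, the other with no effect.** The pooled true difference is the size-weighted mean risk minus 1%.

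| Sizes (IMCP/PSA/control) | Programme at 4.5% | Pooled true difference | Pooled test passes |
|---|---|---|---|
| 102/102/102 | either | (102×4.5 + 102×1)/204 − 1 = 1.75 points | 30.7% |
| 90/109/109 | IMCP | (90×4.5 + 109×1)/199 − 1 = 1.58 points | 28.3% |
| 90/109/109 | PSA | (109×4.5 + 90×1)/199 − 1 = 1.92 points | 21.0% |

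The same test applied to the affected arm alone passes 4.7% of the time (102 v 102), 3.9% (IMCP, 90 v 109) or 4.1% (PSA, 109 v 109).

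**4. Vary the assumptions.** Achieved sizes, IMCP at 4.5%, control at 1%:

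| PSA risk | Pooled test passes |
|---|---|
| 1% | 28.3% |
| 2% | 17.3% |
| 2.75% | 11.6% |
| 3.5% | 7.7% |

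In the other direction, with IMCP at 6% and PSA at 1%, it passes 15.1% of the time.

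**5. A passing data set.** At planned sizes, 4/204 v 1/102 passes, with an upper limit of 3.49 points. If all four events fell in one arm, that arm's own upper limit would be 7.6 points (4/102 v 1/102). Its observed difference would be 3/102 = 2.9 points, still below the margin.

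**6. What per-arm intervals can deliver.** With all risks at 1%, exact power at achieved sizes is 51.8% for IMCP and 60.1% for PSA, and 33.2% that both pass. At 102 per arm the figures are 61.2% for each and 41.3% for both. At achieved sizes with one control event, IMCP passes only with no events: 1/90 v 1/109 already misses the margin.

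**The case against.** Pooling is declared openly and identically in the Power and analysis sections. A reason is given for handling this outcome apart from the models (very low expected incidence), and at about 100 per arm the pooled contrast is the only one with adequate power. The hypotheses are worded for the active interventions jointly, so testing their average is a coherent choice, and the test controls its own error. This stands: nothing is miscalculated or contradictory.

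A reader might infer that the plan will declare each programme safe once the pooled test passes. The text does not say so. The Discussion states an aim, and its notion of safety extends beyond prescribing to other hazards (visit length, physician effort, requests for treatment, physical health), which do go into the three-group models. Nor does calling the pooled contrast primary rule out a secondary per-arm interval, which an analysis plan not shown here may contain.

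The 31% figure needs the second programme to have no effect at all. Both programmes encourage discussion of depression, so fully discordant effects are the extreme case, and step 4 shows how quickly the figure falls.

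What remains is that the only contrast stated for this outcome cannot answer a question about either programme, and the article does not limit its conclusion accordingly.

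**Conclusion.** The pooled test is valid, correctly powered, and informative about the average effect of the two programmes. It does not support a noninferiority statement for PSA or for IMCP. In the illustrative worst case a programme sitting at the margin is covered by a passing result 31% of the time as planned and 21% to 28% at the achieved sizes. With IMCP at 4.5% and PSA at 2% to 3.5%, the range is 17% to 8%. These figures rest on assumed risks, with control at the article's 1%.

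Two stronger readings are not supported. The test's error rate is not wrong: it is about 5% for the hypothesis stated. Nor would a harmful arm usually be visible as an observed excess above 3.5 points. At planned sizes with up to four control events, a passing result cannot contain a single-arm observed difference above 2.94 points. What is exceeded is the arm's true difference or its confidence limit.

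This is a cheap improvement to reporting and interpretation, not a design error.

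**What to change.** - Keep the pooled contrast as the primary noninferiority test, and word its conclusion as applying to the average of the two programmes.
- Add the same two-sided 90% restricted maximum likelihood interval for PSA v control and for IMCP v control, as secondary results read against 3.5 points.
- State that no noninferiority claim for a single programme will rest on the pooled result alone.
- State the per-arm power with these intervals (about 52% for IMCP, 60% for PSA, 33% for both), and that a per-arm limit above the margin means noninferiority was not shown, not that the programme is unsafe.

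I would not make the word 'safe' depend on this one limit. Two harmless programmes would both meet it only one time in three, and the Discussion's idea of safety covers more than prescribing.

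The cost is two further intervals and a few sentences, with no new patients or data. The downside is the low per-arm power: an inconclusive result for at least one programme is likely even if neither does harm.
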